### Module 3: HIV-related stigma and discrimination

If you are HIV-positive, you may face stigma. Let's talk about it

Choose how you feel about each statement. We understand some questions might sound disturbing. Please share your experience. It will help to create a more inclusive environment for everyone

An exit button is always available at the beginning of each module. Respondent can always scroll back to it

☐ OK (click is required)

62. I am not as comfortable as I used to be in dating since I learned I have HIV

- ☐ strongly agree
- ☐ agree
- ☐ disagree
- ☐ strongly disagree
- ☐ I don't know

63. I disclosed my HIV status on my online profile in the main app I'm using

- ☐ yes
- ☐ no

64. If no, is there any reason you don't mention your HIV status? (tick as many as apply)

- ☐ I revealed it before and couldn't meet anybody
- ☐ I'm afraid of rejection
- ☐ I say I am looking for safe sex (like with a condom) and I do not need to tell them my HIV+ status
- ☐ I don't need to mention it
- ☐ I'm undetectable
- ☐ I don't want to mention it
- ☐ other
- ☐ does not apply to me (I disclosed my HIV+ status on my profile)

65. I changed the way I have sex since I know I'm HIV positive

- ☐ yes
- ☐ no
- ☐ I don't know
- ☐ does not apply

66. Since I've known that I'm HIV-positive, I have sex with:

- ☐ people regardless of their HIV status
- ☐ only HIV-positive partners
- ☐ I don't have sex anymore
- ☐ does not apply

67. Some people avoid touching me once they know I have HIV

- ☐ strongly agree
- ☐ agree
- ☐ disagree
- ☐ strongly disagree
- ☐ I don't know

68. People I care about stopped contacting me after learning I have HIV

- ☐ strongly agree
- ☐ agree
- ☐ disagree
- ☐ strongly disagree
- ☐ I don't know

69. I have lost friends by telling them I have HIV

- ☐ strongly agree
- ☐ agree
- ☐ disagree
- ☐ strongly disagree
- ☐ I don't know

70. Telling someone I have HIV is risky

- ☐ strongly agree
- ☐ agree
- ☐ disagree
- ☐ strongly disagree
- ☐ I don't know

71. I work hard to keep my HIV a secret

- ☐ strongly agree
- ☐ agree
- ☐ disagree
- ☐ strongly disagree
- ☐ I don't know

72. I am very careful whom I tell that I have HIV

- ☐ strongly agree
- ☐ agree
- ☐ disagree
- ☐ strongly disagree
- ☐ I don't know

73. People with HIV are treated like outcasts

- ☐ strongly agree
- ☐ agree
- ☐ disagree
- ☐ strongly disagree
- ☐ I don't know

74. Most people believe a person who has HIV is dirty

- ☐ strongly agree

- ☐ agree
- ☐ disagree
- ☐ strongly disagree
- ☐ I don't know

75. Most people are uncomfortable around someone with HIV

- ☐ strongly agree
- ☐ agree
- ☐ disagree
- ☐ strongly disagree
- ☐ I don't know

76. I feel guilty because I have HIV

- ☐ strongly agree
- ☐ agree
- ☐ disagree
- ☐ strongly disagree
- ☐ I don't know

77. People's attitudes about HIV make me feel worse about myself

- ☐ strongly agree
- ☐ agree
- ☐ disagree
- ☐ strongly disagree
- ☐ I don't know

78. I feel I'm not as good a person as others because I have HIV

- ☐ strongly agree
- ☐ agree
- ☐ disagree
- ☐ strongly disagree
- ☐ I don't know

79. In the last 12 months, have you ever been excluded from social gatherings or activities (e.g., weddings, funerals, parties, clubs) because of your HIV status?

- ☐ yes, once
- ☐ yes, several times
- ☐ no
- ☐ I don't know
- ☐ it doesn't apply to me

80. Are you currently taking HIV (antiretroviral) treatment? (choose one)

- ☐ yes
- ☐ no, medication is not available at the clinic or pharmacy
- ☐ no, medication is not affordable for me
- ☐ no, I am unable to collect medications at the clinic or pharmacy
- ☐ no, I cannot tolerate medication side effects or am worried about taking the pills
- ☐ no, I do not feel treatment is needed
- ☐ no, I am worried someone would find out my HIV status
- ☐ no, I am not ready to deal with my HIV infection
- ☐ no, I am worried the healthcare workers would treat me badly or disclose my HIV status without my consent
- ☐ no, I do not qualify for treatment in my country because my CD4s are too high
- ☐ no, for other reasons

81. In the last 12 months, have you been told you have an undetectable viral load or are virally suppressed (“good viral load”)?

- ☐ yes
- ☐ no, I have not had a viral load test in the last 12 months
- ☐ no, I had a viral load test and am waiting for the results
- ☐ no, the virus was detectable/I am not virally suppressed
- ☐ I don't know what viral load or viral suppression are
- ☐ I don't have treatment

82. Living with HIV can open new horizons and positively affects us deep inside. Which of the following have been positively affected by your HIV status (tick as many as apply)

- ☐ My self confidence
- ☐ My self-respect
- ☐ My ability to respect others
- ☐ My ability to cope with stress
- ☐ My ability to better take care of my health
- ☐ My ability to contribute to my community
- ☐ Other
- ☐ None of the above

- ☐ PREV (*clicking here brings the respondent to earlier module in case she/he would like to change*)
- ☐ DONE (*brings the respondent to a thank you message*)

*(Thank you message) see p 12*

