#### c) Sampling strategy, recruitment and voluntary informed consent

The target population of the survey are 18+ year-old LGBTI people. The survey can be accessed using a web [link](#) that will be provided at LGBTI social networks, e.g. the LGBT Foundation social networks, as well as national and regional LGBTI community networks. The survey will be opened for a duration of 3 months. Recruitment will not involve any direct recruitment and is anonymized. Participation in the survey is not incentivised. We are aware of the limitations associated to these voluntary recruitment channels and we are exploring, with LGBTI civil society organisations and UNAIDS teams at country and regional levels, all additional opportunities that could increase the participation of marginalised or remote communities and individuals.

It was considered that participants who are afraid to share information about risk behaviours or HIV status may drop out of the survey or falsify their responses. To successfully survey LGBTI people, these biases are being minimized by obtaining fully informed voluntary consent at the start of the survey from participants and ensuring their absolute confidentiality.

The informed consent of voluntary participants is summarised at the introduction of the survey and the following information is provided through a link:

- a concise description of the survey and the organization conducting it, the survey objectives, the populations being invited to participate;
- a clear indication that participation is voluntary and that participants have the right of withdrawal from the survey at any time, or skip any sensitive question/s;
- a description of the participant's role in the survey, including duration of participation, the general nature of the questions;
- a description of the possible discomforts of participation;
- a description of the benefits to the community that are expected to come from the survey
- a description of how the findings will be made available to the respondents and the LGBTI community
- measures made to protect the privacy and confidentiality of the participant and any information that the person provides;
- documentation that the protocol was reviewed and approved by Research Ethics Review Committee (*to be completed once WHO ERC approval*);
- how the results of the survey will be used. This includes explicitly the possible use of the data for scholar purpose, such as doctoral or post-doctoral productions by the research team

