## I) Sample size

Various population size estimate of the different LGBTI groups are available of most low- and middle-income countries. The present survey does not pretend to collect a statistically representative sampling of these population groups. The modelling, analyses and findings of this survey will be careful in extrapolating conclusions to the entire population groups of a said country. Rather, we would like to provide statistically robust modelling of the correlates of HIV infection of the participants to the survey. This is in line with current practice in surveillance for key populations as it does not aim at a nationally representative sample of a country's population.

We set the minimum *a priori* sample size of 100 respondents per country studied, corresponding to a 0.10 (.90) probability level for a five predictors multiple regression.

The sample size for multiple regressions will vary for each equation in our model. For example, for an anticipated effect size ( $f^2$ ) = 0.15, a desired statistical power level of 0.90 and a probability level of 0.05 (0.95), a regression with five predictors would require a sample size of 116 respondents.

We study the combination of answers at the level of the individuals. Missing data can be estimated with multiple imputations. We use polychoric matrices for ordinal and categorical data. Multiple choice questions will be treated on a case by case basis. Detailed description of statistical methods will be provided with findings.

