**(Thank you message)**

*Thank you very much for your support.*

*Sign up to get the results of this study and participate in future studies, your information is completely anonymous, any IP address is decoupled, encrypted and deleted at the end of the study. [https://lgbt-token.org/research\\_signup](https://lgbt-token.org/research_signup) You may share the survey via: <https://www.research.net/r/LGBTHappinessResearch>*

*Get tested for HIV regularly. For more information: <https://hornet.com/about/know-your-status/>*

(Only participant who answered I'm HIV positive are offered to participate to module 3 below)

exit

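### Q63 on app-profile disclosure has no answer for people without a profile, so they cannot be told apart from profile holders who did not disclose

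*Protocol*

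**What the plan says.** Entry to Module 3 depends on self-reported HIV status alone: "Only participant who answered I'm HIV positive are offered to participate to module 3 below". The routing note under Q45 sends respondents who identify as lesbian or straight directly to Q61, the HIV status question, so they too can reach Module 3.

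Q63 then reads "I disclosed my HIV status on my online profile in the main app I'm using", with yes and no as its only answers. Q64 follows: "If no, is there any reason you don't mention your HIV status? (tick as many as apply". Its one not-applicable option is "does not apply to me (I disclosed my HIV+ status on my profile", which describes the respondent who disclosed.

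Section c) of the protocol recruits by web link through LGBTI social networks "as well as national and regional LGBTI community networks". An app profile is not an entry condition. The same section tells respondents that "participants have the right of withdrawal from the survey at any time, or skip any sensitive question/s", and the sample size section adds: "Missing data can be estimated with multiple imputations".

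The protocol does not define a disclosure rate based on Q63, or a denominator for one.

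**The concern.** Q63 can only be answered meaningfully by someone who has a profile. For a respondent without one, no is the literal answer and skipping is the alternative. Neither identifies that person as a non-user, and no other item in the questionnaire asks about app use. Three different situations (a profile without disclosure, no profile, and an ordinary refusal to answer) are thus spread over two records, a no and a blank.

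Two results are exposed. Any proportion disclosing that is computed from Q63 would be pulled down by non-users who tick no. The reasons in Q64, several of which concern stigma, would be mixed with answers from people who had no profile on which to disclose. Because the survey is anonymous, the missing information cannot be recovered after collection, whatever an analysis plan says about denominators.

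**Working it through.** **What can be reproduced.** The protocol gives no disclosure proportion, target or precision for Q63, so there is no figure to reproduce. What follows is an illustration under stated assumptions.

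**Comparison within the instrument.** Other items make the distinction that Q63 lacks. Q50 separates people who inject but do not share equipment from people who do not inject. Q65, Q66 and Q79, in the same module as Q63, each have a not-applicable answer.

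**Inputs, none of them in the protocol.**
- a = share of Module 3 respondents with an app profile, assumed 0.90 to 0.60 (10% to 40% without one).
- d = true disclosure among profile holders, assumed 0.30.
- s = share of people without a profile who leave Q63 blank, taken as 0, 0.5 and 1.
- Profile holders are assumed to answer correctly, and blanks are dropped.

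**Formulas.**
- Observed yes share = a·d / [a + (1 − a)(1 − s)].
- Share of no answers from non-users = (1 − a)(1 − s) / [(1 − a)(1 − s) + a(1 − d)].

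**No skipping (s = 0).**
- a = 0.90: the yes share is 0.90 × 0.30 = 27%. Per 100 respondents, no = 10 + 90 × 0.70 = 73, and 10/73 = 14% of these are non-users.
- a = 0.60: the yes share is 0.60 × 0.30 = 18%. Here no = 40 + 60 × 0.70 = 82, and 40/82 = 49% are non-users.

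**Half of non-users skip (s = 0.5).**
- a = 0.90: 0.27/0.95 = 28.4%; non-users are 5/68 = 7% of the no answers.
- a = 0.60: 0.18/0.80 = 22.5%; non-users are 20/62 = 32%.

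**All non-users skip (s = 1).** 0.27/0.90 = 0.18/0.60 = 30%. There is no bias, and no non-user is among the no answers.

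**Other values of d.** With a = 0.75 and s = 0, true values of 20%, 40% and 60% read as 15%, 30% and 45%, and non-users make up 29%, 36% and 45% of the no answers. Without skipping, the relative shortfall is always 1 − a, whatever d is.

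**With non-users identified.** Restricting Q63 to profile holders gives a·d / a = d, whatever the value of a.

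**The case against.** A reader might infer that the plan's disclosure rate has the wrong denominator. The protocol does not support that. It names no such rate, says multiple-choice items will be handled case by case, and leaves the detailed methods to be given with the findings. A denominator is properly a matter for the analysis plan. What survives is narrower: no analysis plan can restrict to profile holders if the questionnaire does not identify them.

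A reader might also infer that every non-user is counted as a non-discloser. Skipping is allowed, so some will be blank instead, and the bias falls accordingly. This stands as a limit on the size. It does not remove the problem, since nothing tells non-users to skip and a blank does not mark them as non-users. If blanks are imputed, which the protocol permits but does not require, people without a profile receive a disclosure status that has no meaning for them.

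Nor do the documents show how non-users would answer Q64, or that a no at Q63 is routed there. Documented routing runs between modules, and the option at Q64 for people who disclosed suggests that everyone sees it. Non-users may leave Q64 blank or tick its not-applicable option. The latter, paired with a no at Q63, could be caught by the planned discrepancy flags. That safeguard is partial: it reaches only people who choose that pair, and labels them inconsistent, not non-users.

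Finally, recruitment is online and partly through social networks, so many respondents may hold a profile of some kind, and the 40% end of the range is not grounded in the protocol. It is also tempting to say that country comparisons would partly reflect app use. That is possible, but the protocol has no information on how app use varies.

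**Conclusion.** The concern holds as a defect in one item and its follow-up. As printed, Q63 and Q64 cannot distinguish HIV-positive respondents without a profile from profile holders who did not disclose. Any disclosure proportion computed from Q63 is biased downward to the extent that non-users tick no, and the Q64 reasons are mixed to the extent that those non-users go on to answer Q64.

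The true size cannot be determined from the protocol. The illustrative range, 27% to 18% observed against 30% true, rests on three assumptions: 10% to 40% of respondents without a profile, 30% disclosure among the rest, and no skipping. The matching contamination of the no answers, 14% to 49%, should be quoted as a range and not at its upper end alone.

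This is minor. Module 3 is optional, only two of 82 questions are affected, and neither the sample size nor either of the two main research questions depends on them.

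**What to change.** Add an answer to Q63 for respondents who use no app or have no online profile. Either add the same answer to Q64 or skip these respondents past Q64; the skip is optional and would be new routing within the module. Report Q63 among profile holders, and the Q64 reasons among profile holders who answered no. Do not impute Q63 for people who chose the new answer.

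The cost is one short answer option translated into the survey languages. No question is added.

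### Module 3: Q66 has no answer for HIV-positive respondents whose partners are all HIV-negative, and Q62 none for those who do not date, so neither group can be separated in the results

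*Protocol*

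**What the plan says.** Module 3 follows the HIV status question (Q61). The note after the thank-you message says who sees it: "Only participant who answered I'm HIV positive are offered to participate to module 3 below". There is no further filter on dating or sexual activity.

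**Q66** has the stem "Since I've known that I'm HIV-positive, I have sex with" and four answers: "people regardless of their HIV status", "only HIV-positive partners", "I don't have sex anymore" and "does not apply". It carries no instruction allowing several answers, unlike Q64 and Q82, so I read it as single choice.

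**Q62** reads "I am not as comfortable as I used to be in dating since I learned I have HIV". It offers four levels of agreement plus a don't-know answer. In the same module Q65 and Q66 offer "does not apply" and Q79 offers "it doesn't apply to me".

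Section (c) lets respondents skip sensitive questions. Section (l) says that missing data can be multiply imputed and leaves the detailed methods to the reporting of findings. No indicator, coding rule or figure is stated for either item.

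**The concern.** A closed question needs a true answer for everyone who is asked it. Take a person living with HIV whose only partner since diagnosis is HIV-negative. The second Q66 answer is false for that person, and so is the third. The first describes indifference to status, which may not be how the person chooses partners. The not-applicable answer is untrue, because the question does apply. Whichever is ticked, that category then holds two kinds of people, and any comparison of Q66 with stigma or viral suppression is harder to read.

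Q62 asks for a comparison of dating before and after diagnosis. A person in a couple since before diagnosis, or one who does not date, has no such comparison to make. A don't-know answer is not equivalent, because this person is not uncertain.

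Answer options are fixed when the form goes live. Responses are anonymous, and section (o) says that participants cannot be given further direct information afterwards. A later analysis plan can choose a denominator, but it cannot recover a distinction that the form did not record.

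**Working it through.** The plan states no figure for Q62 or Q66, so there is none to reproduce. The check has three parts.

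**1. Do other items recover the distinction?**

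| Item | What it records | Why it falls short |
|---|---|---|
| Q36 (Module 1) | Relationship situation | Gives neither the partner's HIV status nor the duration of the relationship, and does not ask about dating |
| Q48 (Module 2) | HIV status of the last anal sex partner where no prevention method was used | Leaves out couples protected by condoms, PrEP or an undetectable viral load; respondents answering lesbian or straight at Q45 bypass Module 2 |
| Q51 (Module 2) | Reaction to a potential partner who discloses being HIV-positive | Concerns attitude, not the status of actual partners; same routing limit |

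They help in part, but none replaces the missing answers.

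**2. Q66: how far can the first share move?** Let R be the true share who have sex regardless of status, and g the share whose partners are all HIV-negative. Let m be the fraction of that group who tick the *regardless* answer; the rest tick not applicable.

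Reported share = (R + g·m) / D

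D = 1 if not-applicable answers stay in the denominator, and D = 1 − g(1 − m) if they are removed. Skipping acts like removal. Other uses of the not-applicable answer are ignored. R = 40% and g = 5% to 20% are assumptions, not document values.

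| | g = 5% | g = 10% | g = 20% |
|---|---|---|---|
| All tick *regardless* (m = 1) | 45.0% | 50.0% | 60.0% |
| Half do (m = 0.5), rest kept | 42.5% | 45.0% | 50.0% |
| Half do (m = 0.5), rest removed | 43.6% | 47.4% | 55.6% |
| None do (m = 0), all kept | 40.0% | 40.0% | 40.0% |
| None do (m = 0), all removed | 42.1% | 44.4% | 50.0% |

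Example for g = 10%, m = 0.5, rest removed: (0.40 + 0.05) / (1 − 0.05) = 0.45 / 0.95 = 47.4%.

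Against the all-respondent share of 40%, the excess runs from 0 to g. In this model it is never negative, but it can be zero.

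**3. Q62: direction.** Let A be agreement among daters, d the share of non-daters, and a the agreement recorded among non-daters.

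Reported agreement = (1 − d)·A + d·a

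With A = 50% and d = 10% to 30% (both assumed):

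| Non-daters' behaviour | d = 10% | d = 20% | d = 30% |
|---|---|---|---|
| All disagree, or answer don't know and are kept | 45% | 40% | 35% |
| All skip, or answer don't know and are removed | 50% | 50% | 50% |
| All agree | 55% | 60% | 65% |

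For example, at d = 30% with all disagreeing: 0.7 × 0.5 = 35%. With all agreeing: 0.35 + 0.30 = 65%. The sign depends on behaviour that the form does not reveal.

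If non-daters skip, or their don't-know answers are set to missing, the multiple imputation that section (l) permits could give them a dating-comfort value that does not exist.

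**The case against.** **Respondents are not forced into the first answer.** They can choose not applicable or skip. This stands. A reader might infer that the *regardless* share is overstated, or overstated by the whole affected group. The documents do not support that: full inflation is only the m = 1 row, and with m = 0 and all answers kept there is none.

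**The first answer may be defensible.** Its contrast is with restricting sex to HIV-positive partners, and a person with a steady HIV-negative partner has not done that. This has some force. But the wording describes indifference to status, and respondents cannot be expected to read it all in one way.

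**Other items touch on the subject.** A reader might take Q66 as the only question on partners' HIV status put to HIV-positive people. Q48 and Q51 show otherwise, and Q36 allows a split by relationship situation. None of them separates the two groups at issue.

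**Q62 need not be biased downward.** This stands. A reader might assume that non-daters disagree and so lower the dating-stigma share. They may equally agree, answer don't know or skip.

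**Denominators belong to an analysis plan that is not shown, and neither item is a stated outcome.** Both are true, and the missing coding rule is not the point here. The point is the option lists, which the Protocol itself fixes. The two research questions in the data analysis section do not name Q62 or Q66, which limits the importance.

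**Conclusion.** Both gaps hold on a plain reading of the form. Q66's answers are not exhaustive: its first share may be too high, by between zero and the share of respondents whose partners are all HIV-negative, and its not-applicable category may include sexually active people to whom the item applies. Q62 cannot separate non-daters, so its share can rest on a mixed denominator, with bias of unknown size and direction.

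The Protocol gives none of the group sizes. The illustrated excess of 0 to at most 5 to 20 points in Q66, and the 35% to 65% spread around an assumed 50% in Q62, rest wholly on assumed inputs. They show what is possible and do not predict a result.

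This is a minor point. It affects descriptive Module 3 results and any association built on these two items. It does not touch a named primary outcome.

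**What to change.** Before the survey opens:

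- **Q66:** add *only HIV-negative partners*. An option for one steady partner should not be added alongside it, because it would overlap with the options defined by partner status.
- **Q62:** add *does not apply (I do not date)*. Report the item among those to whom it applies, and do not impute a value for the others.

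The cost is two answer options and their translation from English into the 16 other listed languages. Comparability with any earlier use of the items falls slightly, which matters a little because the questionnaire section prefers items with demonstrated validity. Q62 would also depart from the five-answer format that it shares with Q67 to Q78. The questionnaire was already revised in pre-testing by expanding response sets, so a change of this kind fits the plan's own process.

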# Abstract

**Background** Worldwide, lesbian, gay, bisexual, transgender and intersex (LGBTI) people contend with high risks for HIV infection, stigma and discrimination, and for exclusion from HIV and other health services. In many low- and middle-income countries, LGBTI people are often hidden, marginalised and difficult to assess as part of general population-based surveys. Thus, assessing their exposures and outcomes and burden of HIV disease is extremely challenging. This presents a dilemma for HIV surveillance as their omission from surveillance systems leaves significant gaps in our understanding of HIV epidemics.

**Objective** This research project is aimed at conducting an observational, non-interventional, global cross-sectional internet survey in LGBTI participants to examine how various demographic, economic, socioecological, homophobic, psychosocial, attitudinal and behavioural variables potentiate HIV risk behaviour. We likewise aim to examine self-reported HIV prevalence, exposure to HIV related stigma and discrimination, and to study the association between these socioecological parameters and HIV care and treatment coverage in the survey participants.

**Methods** We imply internet sampling method to conduct the cross-sectional survey recruiting consenting adult LGBTI participants. We select internet sampling for it demonstrated to be particularly useful for hard-to-sample populations, higher number of respondents among hard-to-reach populations, faster recruitment, lower operational cost, greater level of anonymity and security provided to participants. Acknowledging selection bias, we may apply techniques, e.g. prediction modelling, to correct for the bias that results from differential access to, and use of, the internet. To safeguard the data privacy, rights and welfare of the research participants, the access to the online survey will be provided via anonymous weblink. The survey will be opened for three (3) months. Our cross-sectional study is observational by nature and it does not alter the exposure status of the consenting respondents and thus warrants minimal to no risk for the participants. We will examine the outcome and the exposures in the target population and will study their association. Our survey questionnaire provides essential components to fulfil the above objective and was developed using selected standard protocols.

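### Q67-69 on enacted HIV stigma presuppose that others know the respondent's status, but offer no 'nobody knows' answer, and no item records whether anyone knows

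*Protocol*

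**What the plan says.** The Abstract of the protocol lists "exposure to HIV related stigma and discrimination" among the things to be examined. It also aims to relate the socioecological parameters to HIV care and treatment coverage.

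Appendix 1 routes on self-reported status alone: "Only participant who answered I'm HIV positive are offered to participate to module 3 below". Within Module 3, three items concern how others reacted:

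- Q67: "Some people avoid touching me once they know I have HIV"
- Q68: "People I care about stopped contacting me after learning I have HIV"
- Q69: "I have lost friends by telling them I have HIV"

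Each has four levels of agreement plus 'I don't know'. Q79, on exclusion from social gatherings, adds "it doesn't apply to me", and Q64, Q65 and Q66 also have a not-applicable choice.

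Two kinds of item come near to disclosure. Q63 reads "I disclosed my HIV status on my online profile in the main app I'm using". Q71 reads "I work hard to keep my HIV a secret", and Q72 asks about care in choosing whom to tell.

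Section c) lets respondents skip sensitive questions. The Sample size section allows multiple imputation of missing data and defers the detailed statistical methods. No scoring rule is given for Q67-69 or for 'I don't know'.

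**The concern.** A person whose HIV status is known to nobody cannot have been avoided, dropped or rejected because of it. Such a person still receives Q67-69 and has no answer that says so. Disagreement then has two meanings: people know and did not react badly, or nobody knows. 'I don't know' likewise mixes real uncertainty with the question not applying.

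This is not a gap that an analysis plan can close. The variable that separates the two groups is never collected, and respondents are anonymous and cannot be contacted again (section o).

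The ambiguity bears on a stated aim. Q80 offers worry that someone would find out one's HIV status as a reason for not being on treatment, so the questionnaire itself links concealment with treatment. Results are also meant for country dashboards and, possibly, annual trends. If disclosure differs between countries or over time, differences in Q67-69 may partly reflect that.

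**Working it through.** The protocol states no figure on this point, so there is none to reproduce. The check has two parts.

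**1. Can the undisclosed be identified from other items?**

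| Item | What it records | Does it show whether anyone knows? |
|---|---|---|
| Q63 | Disclosure on the profile of the main app | No: family, friends and other contacts are not covered |
| Q64 | Reasons for not disclosing on that profile | No: same restriction |
| Q71 | Effort at secrecy | No: fits having told nobody or a few people |
| Q72 | Care over whom to tell | No: same |

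None of them separates the groups, and none routes respondents past Q67-69.

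**2. How far could the observed rate move?**

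Inputs, all assumed because the documents give none:

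- *p*: share agreeing among those whose status is known (20%, 40%, 60%)
- *u*: share whose status nobody knows (10%, 30%, 50%)
- *w*: share of the undisclosed who disagree; the rest choose 'I don't know' or skip and are treated as missing (0, 0.5, 1)

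The undisclosed contribute no agreement, and only those who disagree enter the denominator:

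observed = p(1 − u) / [(1 − u) + u·w]

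Example with p = 40%, u = 30%:

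- w = 0: 0.28 / 0.70 = 40%
- w = 0.5: 0.28 / 0.85 = 32.9%
- w = 1: 0.28 / 1.00 = 28%

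| p | u | w = 0 | w = 0.5 | w = 1 |
|---|---|---|---|---|
| 20% | 10% | 20% | 18.9% | 18% |
| 20% | 30% | 20% | 16.5% | 14% |
| 20% | 50% | 20% | 13.3% | 10% |
| 40% | 10% | 40% | 37.9% | 36% |
| 40% | 30% | 40% | 32.9% | 28% |
| 40% | 50% | 40% | 26.7% | 20% |
| 60% | 10% | 60% | 56.8% | 54% |
| 60% | 30% | 60% | 49.4% | 42% |
| 60% | 50% | 60% | 40.0% | 30% |

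At w = 1 the observed rate is p(1 − u), a relative understatement of exactly u. At w = 0 there is none.

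**Comparing two countries.** Assume country A has p = 40%, u = 10%, and country B has p = 50%, u = 40%.

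- w = 1: A = 0.40 × 0.90 = 36%; B = 0.50 × 0.60 = 30%. The order is reversed.
- w = 0.5: A = 0.36 / 0.95 = 37.9%; B = 0.30 / 0.80 = 37.5%. Practically equal.
- w = 0: 40% and 50%. The order is right.

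With u between 10% and 40% and w = 1, a reversal needs true rates that differ by less than a factor of 0.90 / 0.60 = 1.5.

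**The case against.** The strongest objection concerns the quantity being estimated. Someone whose status nobody knows has not been exposed to these reactions, so disagreement is a true report. Prevalence among all HIV-positive respondents, p(1 − u), is a legitimate measure of exposure. That stands, and it is why both figures should be reported. It does not remove the problem: the observed rate equals p(1 − u) only if every undisclosed respondent disagrees. If some choose 'I don't know' or skip, it falls between p(1 − u) and p, and the data cannot show where. Imputing those answers from respondents whose status is known would assign an experience that could not have occurred.

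A reader might infer that people who keep HIV secret will be scored as unstigmatised. The protocol does not establish this, since it gives no scoring rule and both 'I don't know' and skipping are available.

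A reader might also take Q67-69 to be the only items without a not-applicable choice. They are not: Q62 and Q70-78 use the same five options. The difference is that those items do not require others to know.

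Three further points carry weight. Fear and concealment are partly captured by Q70-72, which can serve as imperfect proxies. The first two research questions concern homophobic climate and social and economic inequality, not enacted HIV stigma. The protocol also asks for a short questionnaire built on validated questions. These limit the importance of the point and argue for a small change that leaves Q67-69 intact.

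**Conclusion.** The point holds as a defect of measurement with an uncertain effect. Q67-69 are put to every HIV-positive respondent in Module 3, they presuppose that others know, and nothing in the questionnaire identifies those for whom that is untrue. Enacted stigma among people whose status is known may be understated by a relative amount between zero and the undisclosed share. That share is not in the documents, and the percentages above rest entirely on assumed values of p, u and w.

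Comparisons between countries may mix stigma with disclosure, and under some assumptions the order can reverse. The same mixing may affect the association with treatment coverage. A reader might go on to conclude that this association would be weakened or reversed. The documents do not support that: the country example does not involve treatment, and the direction depends on how concealment relates to treatment among the respondents, which is unknown.

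This is a cheap improvement worth making before data collection, because it cannot be repaired afterwards.

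**What to change.** Before Q67 add one item: 'Does anyone other than health workers know you are HIV-positive? (tick as many as apply: yes, I told them / yes, without my choice / no / don't know)'. Keep the wording of Q67-69.

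Then:

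- report Q67-69 among all HIV-positive respondents and also among those whose status is known;
- for Q67 and Q68, define the second group by any 'yes'; for Q69, include only those who told someone, since the item asks about losing friends by telling them;
- give the share answering 'no' beside these results;
- do not impute Q67-69 for respondents answering 'no'.

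The cost is one more item for HIV-positive respondents, its translation, and a short scoring rule. The filter is not perfect: someone who told a partner but no friends still passes it for Q69.

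A lighter alternative is a 'nobody knows / does not apply' answer on each of Q67-69. It adds no question, but it changes the response set and does not distinguish people who told someone from those whose status became known without their choice.
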